###### Cognitive State

The Montreal Cognitive Assessment will be used to assess cognition in people with dementia. The instrument has 30 items in 8 domains of cognitive functioning: attention and concentration, executive functions, memory, language, visuoconstructional skills, conceptual thinking, calculations, and orientation. In total, 0-30 points can be obtained, and lower scores indicate a higher degree of cognitive impairment [46,47].

###### Depressive Symptoms

The Geriatric Depression Scale will be used to assess depressive symptoms in people with dementia. The scale has 15 items (yes/no answers). In total, 0-15 points can be obtained, and higher scores indicate a higher level of depressive symptoms [48-50]. For the relatives, the Center for Epidemiological Studies Depression Scale will be used. The scale has 20 items (4-point Likert scale), and a total of 0-60 points can be obtained. Higher scores indicate a higher level of depressive symptoms [51,52].

###### Acceptance and Usability

The Technology Usage Inventory will be used to measure acceptance in all included participants. It captures technology-specific and psychological factors that contribute to the use of a technological device. The instrument includes 8 main dimensions (curiosity: 4 items; anxiety: 4 items; interest: 4 items; usability/user-friendliness: 3 items; immersion: 4 items; utility: 4 items; skepticism: 4 items; and accessibility: 3 items) with 30 items in total (7-point Likert scale). For every dimension, 1-21 or 28 points can be obtained. Furthermore, the instrument includes a ninth dimension (intention to use with 3 items). This ninth dimension is measured on a visual analog scale, including a 10-centimeter long horizontal line with two endpoints (agree and disagree). A cross on the line indicates the degree of agreement. For the evaluation, the distance from the right endpoint (disagreement) to the answer across the line is measured. This distance (in millimeters) is determined and summed up for all 3 items (maximum: 300, minimum: 0). For all 9 dimensions, higher levels on the respective dimension indicate a higher level of expression in the respective construction [53].

###### Affect

The Positive and Negative Affect Schedule will be used to measure effect of the relatives. The instrument has 20 items (5-point Likert scale) with two dimensions (positive affect and negative affect). In total, 20-100 points can be obtained, and higher scores indicate higher positive or rather negative affect [54].

###### Behavioral Problems

The Neuropsychiatric Inventory (NPI) will be used to measure behavioral problems of people with dementia, and information will be obtained from a caregiver who is familiar with the patient’s behavior. The instrument has 12 domains (delusions, agitation/aggression, depression, anxiety, elation/euphoria, apathy/indifference, disinhibition, irritability, aberrant motor behavior, sleep and night-time behavior disorders, appetite, and eating disorders). The NPI assesses the presence, frequency, and severity of each behavior in the previous month, as well as the level of caregiver distress as a result of each of the neuropsychiatric problems. The domain score is obtained by multiplying the frequency and severity scores. The total NPI score is finally the sum of all individual domain scores (thus, ranging from 0-144). The caregiver distress level is not part of the total NPI score. Higher scores indicate greater psychopathology [55,56].

###### Sensor Data

Furthermore, sensor data from the robot platform Pepper and the theratainment app will be continuously collected during the study period. The objective is to extract key features from the sensor data and investigate correlations with the scores from the used questionnaires (AES, Montreal Cognitive Assessment, and TUG) to apply advanced machine learning techniques to research the potential of developing statistics-based estimators to predict motivation, cognitive state, and mobility/physical activity.

##### Qualitative Measurements

Open, semistructured observation of people with dementia interacting with the robot at home will be conducted by professional caregivers to explore how they handle the robot during the study period. Besides individual interviews with the people with dementia and relatives, focus groups will also be organized with the professional caregivers and dementia trainers to obtain more in-depth knowledge about their experience with the robot.

###### Data Management

The sensor data of robot Pepper will be processed directly for the interaction and not be stored. A connection to Pepper from outside (eg, tablet PC–based training program) is only possible via a secure connection and with a user ID or password. During the study, sensor data is immediately forwarded to the appropriate project partners for processing via secure connections. All sensor data are analyzed anonymously and result in anonymized feature data. The videos themselves are deleted immediately after extracting the features. For each completed dementia training exercise, the tablet PC stores data reflecting the performance of each participant with dementia (eg, wrong/correct answers, quizzes, and time). All data will be analyzed anonymized.

The questionnaires and interviews will be handed over by project members of the social nonprofit organization either personally or via a secure server (protected password) to the Medical University. All personal data of participants will be treated confidentially and interviews will be anonymized during transcription. All participants will be assigned a code. The Medical University and Joanneum Research (research partner) have access to the final data set for analysis. To ensure data quality, all data from paper-pencil questionnaires will be entered into the statistical software by one researcher and will be scanned for errors after data entry by the same person. Furthermore, sample checks for data errors by a second researcher are planned, and the statistician will also perform a plausibility check of the data before starting the analysis.

### Analysis

#### Quantitative Analysis

Statistical analyses of the results will be performed following the intention-to-treat principle. Descriptive statistics of the data will be presented as a mean and standard deviation, or median and quartile, depending on the nature of the distribution. To describe categorical data, absolute and relative frequencies will be used. To answer the primary question as to whether the motivation differs between the two intervention groups, a median regression is planned. Therefore, it can be adjusted for the degree of dementia and depression. For differences between the intervention groups for the secondary outcomes, the ordinal scale data will be analyzed with median regression. For metric data, a covariance analysis is planned, which also adjusts to degrees of dementia and depression. Changes in pre- and postintervention outcomes concerning relatives will be analyzed by a paired *t* test or a two-tailed Wilcoxon signed-rank test, depending on the distribution of the data. For the sensor data, correlations with the scores of questionnaires will be performed. Furthermore, a skeleton-based analysis of human activity will be applied on the video frames of the physical exercises [57]. The estimated increase of kinetic energy of the movements is intended to provide cues for the increase of motivation [58]. In addition, the video data will be analyzed for nonverbal expressive features which provide analytics about the state of mobility. The significance level will be set to alpha=0.05. For the evaluation, SAS 9.4 (SAS Institute Inc, Cary, North Carolina, United States) will be used.

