### Sample Size

There are currently no comparative studies investigating the influence of humanoid robots on the motivation of people with dementia. Therefore, no results can be used to calculate an optimal sample size. However, to gain insight about what is feasible with our sample size, we estimated the possible effect size. For simplicity, sample size considerations are based on a Student’s *t* test. A sample size of 20 in each group will have 80% power to detect an effect size of 0.91 using a two-group *t* test, with a 5% two-sided significance level. For example, if there is a mean difference of 10 between the groups and a standard deviation of 11 (the latter being assumable according to the literature [32]), the effect size would be 0.91. As a drop-out rate of 20% to 30% can be assumed, 20 people with dementia per group was planned (40 in total). This is the maximum number of people that can be realized with two robots during the study period of 10 months. Beside the people with dementia, their main relatives will be included (n=40, 20 each group) and as a supplement five nurses, nursing assistants, and dementia trainers, respectively, will be included. A small sample size of nursing staff and dementia trainers were chosen because a minimum of three people are necessary for usability tests (which is one focus in the study), if there are more than three groups included [33]. The inclusion of these further two groups was necessary to get an in-depth understanding of using robots in home care.

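### The 80% power figure is for a t test; for the planned median regression it is optimistic, at about 50-60% if AES scores are roughly normal and covariates earn no credit

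*Protocol article*

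**What the plan says.** Under Sample Size, the article says no comparative results exist from which to derive an optimal number, so it works out what effect the available number could detect. The basis is declared: "For simplicity, sample size considerations are based on a" Student's t test. The result is "A sample size of 20 in each group will have 80% power to detect an effect size of 0.91", "with a 5% two-sided significance level". The illustration is "if there is a mean difference of 10 between the groups and a standard deviation of 11". The same section expects 20% to 30% drop-out and says that 40 people is the most that two robots can serve in the study period.

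Under Quantitative Analysis, the primary analysis is a different method: "To answer the primary question as to whether the motivation differs between the two intervention groups, a median regression is planned". The next sentence adds: "Therefore, it can be adjusted for the degree of dementia and depression". For secondary outcomes, that section assigns ordinal data to median regression and metric data to covariance analysis with the same adjustment. The AES is described under Motivation as 18 four-point items with a total from 18 to 72. No power or detectable difference is given for median regression.

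**The concern.** The power statement concerns a difference in means tested by a t test. The planned analysis concerns a difference in medians. The two do not have the same precision: for normal data the sample median has 2/π = 64% of the efficiency of the mean, and in small samples the standard error of a median is itself hard to estimate. Substituting a t test therefore errs in the optimistic direction unless the scores have heavy tails.

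The purpose of the calculation is to tell readers what 20 per group can show. If it overstates this, a non-significant primary result is more likely to be misread as evidence of no worthwhile effect. The sample cannot grow, so an honest figure for the planned method matters more than usual.

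**Working it through.** **Inputs from the article.** 20 per arm; two-sided 5%; difference 10; SD 11, so d = 10/11 = 0.909 (stated as 0.91); drop-out 20-30%, so 20 × 0.8 = 16 or 20 × 0.7 = 14 analysed per arm. **Assumptions added here:** normal scores with equal SD, and no credit for covariates.

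**1. Reproduce the stated figure.** SE of the mean difference = 11 × √(2/20) = 3.48, so the noncentrality is 10/3.48 = 2.87. The noncentral t with 38 df gives 80.0% (80.1% at d = 0.91). The article's figure is right for a t test.

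**2. Same inputs, median regression, large-sample formula.** The variance is multiplied by π/2. SE = 11 × √(π/2 × 2/20) = 4.36, so the noncentrality is 10/4.36 = 2.29.
- Normal approximation: Φ(2.29 − 1.96) = 63%.
- Noncentral t, 38 df: 61%.

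**3. Simulation at 20 per arm.** The article does not name the inference method, so several were tried.

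| Method, normal data, 10 points, SD 11 | Power |
|---|---|
| t test | 80% |
| Median regression, bootstrap SE | 60% |
| Median regression, sparsity-based SE | 57% |
| Median regression, rank-score test | 52-53% |
| Median regression, Wald test, separate run | 47% |

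The true SE of the median difference at n = 20 is 4.21, slightly below the formula's 4.36. A test that knew this SE would have 64-66% power. The shortfall below 61% therefore comes from the inference procedure, including the need to estimate the SE.

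**4. Detectable difference at 80% power, 20 analysed per arm.** By formula, 0.909 × √(π/2) = 1.14 SD, or 12.5 points. Simulated power there is only 73-78%, and 80% is reached nearer 1.15-1.25 SD: 1.15 × 11 = 12.7 and 1.25 × 11 = 13.8 points. With the Wald test (68% at 1.14 SD) it would be larger still. To detect 10 points, the formula needs about 30-31 analysed per arm.

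**5. With the stated drop-out (a separate loss).** At 16 or 14 per arm the t test has 70% or 64%, and median regression by formula has 51-54% or 46-48%. The formula's detectable difference is 1.28 SD (14.1 points) or 1.38 SD (15.2 points). Given step 4, these are likely to be on the low side.

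**6. Sensitivity to distribution (formula, 20 per arm, d = 0.91).**

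| Scores | Efficiency against the mean | Power |
|---|---|---|
| Uniform | 0.33 | 37% |
| Normal | 0.64 | 61% |
| Logistic | 0.82 | 72% |
| t, 5 df | 0.96 | 78% |

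For a Laplace distribution the efficiency is 2, so the median would do better than the mean.

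**7. Sensitivity to covariates.** Adjusted median regression in simulation (normal data, sparsity-based SE) gave 47% if the covariates explain nothing, 58% at R² = 0.2 and 73% at R² = 0.4. By formula, R² of about 0.37 restores 80%. The article states no R².

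**The case against.** A reader might infer that the article claims 80% power for its median regression. It does not: it names the t test and calls it a simplification. Nor does the sample size rest on the figure. The 10/11 pair is only an example, the aims are worded as exploratory, and 40 is the logistical maximum. A corrected figure would not change the number recruited. These points stand, and they lower the severity.

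A reader might also take 50-60% as the power of the planned analysis. That is too strong. No section says that AES scores are normal; normality enters only through the t test. The planned adjustment could recover power by an amount the article gives no means of judging. It would help a covariance analysis too, however, so it does not remove the relative loss under normality.

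Finally, a reader might conclude that median regression is the wrong method. The article does not support this. A sum of Likert items can defensibly be called ordinal, and the choice then agrees with the article's rule for secondary outcomes. The mean and SD under Sample Size point towards metric treatment, but choosing between them is partly preference.

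What survives is narrower: disclosing that a t test was used does not tell the reader that the substitution is optimistic, or by how much.

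**Conclusion.** The mismatch is real, and the stated feasibility figure is optimistic for the planned test. With 20 analysed per arm, a 10-point difference, SD 11, normal scores and no covariate credit, power is about 50-60% in most simulations (61-63% by formula) rather than the t test's 80%. The detectable difference is about 1.15-1.25 SD rather than 0.91 SD. The size of the gap depends on the shape of the AES distribution, the strength of the covariates and the inference method, none of which the article fixes, so a range is the right form. This is a should-fix item: the t-test arithmetic is correct and openly labelled, and the sample size would not change.

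**What to change.** Under Sample Size, keep the t-test figure if wished, but add the power and detectable difference for median regression, obtained by simulation with the inference method that will be used. On present inputs this is about 50-60% at 10 points, or a detectable difference of about 1.15-1.25 SD (roughly 12.5-14 points) at 20 analysed per arm, and larger at 14-16. State the distributional assumption and that no credit is taken for covariates. Do not substitute the formula value of 1.14 SD as an 80% figure, because it falls short of 80% at this sample size. The cost is a short simulation and a few sentences.

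Alternatively, if the AES total is accepted as metric, make the covariance analysis already planned for metric data the primary analysis, adjusted for baseline AES, degree of dementia and depression, with median regression as a sensitivity analysis. The t-test figure would then be a reasonable unadjusted guide. The cost is higher: the estimand changes from a median to a mean, and the result becomes somewhat more sensitive to outliers, though the 18-72 range limits this. Because the Results section reports that some participants have already finished the intervention, this route needs a dated, justified amendment before any unblinded analysis.

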**Methods:**

A mixed methods study will be performed, including a randomized controlled, parallel, 2-arm study with a complementary qualitative part. This sample includes 40 PWD living at home and 40 relatives, each complemented with five professional caregivers and dementia trainers. The intervention group will receive Coach Pepper (a SAR connected with a tablet PC–based dementia training program), and the control group will receive exclusively tablet PC–based training without the SAR. The duration of the intervention will be three weeks per household. Data will be collected at baseline and during and after the intervention by standardized questionnaires, sensor data of the robot, and tablet PC, as well as semistructured interviews, focus groups, and observation.

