### Randomization and Blinding

A randomization plan will be prepared by the Institute of Medical Informatics, Statistics and Documentation at the Medical University of Graz. For that, randomization software will be used. Only authorized people will be able to randomize patients, and the allocation to the intervention and control group will be balanced. There are two robots available for simultaneous use in the study, therefore, four people will always be randomized (two for intervention and two for the control group) two weeks before the next round starts. This will be done until all 40 people have been randomized. A single blinding will be performed. The clinical health care psychologist who will perform data collection before and after the interventions will be blinded.

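### The primary median regression does not name baseline AES as a covariate, leaves open whether AES is a post value or a change, and does not tie its two covariates to baseline

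*Protocol article*

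**What the plan says.** The Quantitative Analysis section of the protocol article plans a median regression to compare motivation between the two groups, and adds: "Therefore, it can be adjusted for the degree of dementia and depression". For metric secondary outcomes, "a covariance analysis is planned, which also adjusts to degrees of dementia and depression". For ordinal secondary outcomes it names median regression without restating covariates. No model is said to include the baseline value of its own outcome.

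The abstract states: "Data will be collected at baseline and during and after the intervention by standardized questionnaires". The time schedule (Table 1) marks questionnaires in the week before and the week after each three-week round, and Randomization and Blinding has a blinded psychologist collecting data before and after. A baseline AES therefore appears to be available. The instrument-by-instrument schedule in Multimedia Appendix 1 is not shown.

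The outcome is described in two ways. Under Primary Outcome Measurements it is the AES total (18 to 72 points). The Primary Aims and the hypothesis speak of apathy that rises, falls or stays stable, which suggests change. The analysis text does not choose.

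Depression (Geriatric Depression Scale) and cognition (Montreal Cognitive Assessment) in people with dementia are both listed as secondary outcomes. The Mini Mental State Examination appears as an inclusion criterion.

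**The concern.** The article goes as far as naming covariates, and the two it names are correlates of apathy rather than the pre-treatment apathy score itself. Three weeks apart, a person's own earlier score would usually be expected to predict the later one at least as well as dementia severity or depression does. The sample is fixed at 40 by the two available robots, so the analysis is one of the few places left to gain precision.

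Two ambiguities add to this. Post value and change have different variances and use baseline differently, so the primary estimate is not pinned down. And nothing restricts depression or degree of dementia to baseline. The Background section expects motivation-oriented interventions to lower depression as well as apathy. If the post-intervention depression score were used, the model would condition on something treatment may change and could remove part of a real effect.

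**Working it through.** **Inputs from the Sample Size section.** "A sample size of 20 in each group will have 80% power to detect an effect size of 0.91", "with a 5% two-sided significance level"; "if there is a mean difference of 10 between the groups and a standard deviation of 11". The basis is an unadjusted two-group t test.

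**Plan's own figure.** d = 10/11 = 0.909. Noncentrality = 0.91 × √(20/2) = 2.88 on 38 df gives power 0.801. The stated 80% reproduces.

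**Assumed inputs.** The article gives no baseline-to-post correlation r, so a range is used. For the planned model, dementia and depression are each assumed to correlate 0.3 with AES.

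**Step 1: gain over the planned model, median regression.** The simulation used a least-absolute-deviation fit, 10 rounds of 2 + 2, SD 11 and normal errors.

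| r | SE with dementia and depression | SE after adding baseline AES | Change in SE |
|---|---|---|---|
| 0.3 | about 4.1 | 4.1 | none |
| 0.5 | about 4.1 | 3.7 | 1 − 3.7/4.1 = 10% lower |
| 0.7 | about 4.1 | 3.0-3.1 | 1 − 3.1/4.1 to 1 − 3.0/4.1 = 24-27% lower |

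Large-sample check, taking the two covariates as uncorrelated with each other and each correlated 0.3 with AES at both times:
- The SE of a median contrast under normal errors is √(π/2) × 11 × √(2/20) × √(residual variance fraction) = 4.36 × √(fraction).
- Two covariates: fraction 1 − 2 × 0.09 = 0.82, so SE 3.95.
- Adding baseline: the partial correlation is (r − 0.18)/0.82, that is 0.15, 0.39 and 0.63. The fraction 0.82 × (1 − partial²) is 0.80, 0.70 and 0.49. The SEs are 3.9, 3.6 and 3.1.

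The pattern agrees with the simulation, which runs slightly higher in places, as expected with 40 people.

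**Step 2: the same question in a linear model.** If the two planned covariates explain 20% of the variance and the full set 30% to 60% (assumed), the effect detectable with 80% power at 20 per arm moves from 0.81 SD to between 0.76 and 0.58 SD.

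**Step 3: if AES is analysed as change.** With equal variances before and after, the variance of change is 2(1 − r)σ². With baseline as covariate it is (1 − r²)σ². The ratio is (1 + r)/2, so the reduction is (1 − r)/2: 35% at r = 0.3, 25% at 0.5, 15% at 0.7. Adding baseline therefore helps on either reading. Once baseline AES is in the model, subtracting it from the outcome shifts only its own coefficient. The treatment coefficient is then the same for post value and change, in median regression as in least squares, so naming baseline AES also removes the first ambiguity.

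**Step 4: cost.** One parameter, against 40 randomised or 28 to 32 after the assumed 20% to 30% drop-out.

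**The case against.** This is a condensed article, and a fuller protocol or analysis plan may complete the covariate list; the wording says only that the model can be adjusted. That stands as a reason for restraint: the article does not exclude baseline AES, it fails to name it. But it does commit to two specific covariates, and what it commits to is improvable.

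The hypothesis reads like change, in which case baseline is already partly used. This also stands, and it means one cannot say that chance baseline imbalance necessarily carries straight into the estimate. Step 3 shows a gain remains.

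That depression would be taken after treatment is nowhere stated. Correct: it is an unclosed possibility, not a stated error.

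Three stronger readings are tempting and not supported:
- *That the randomisation round is another source of free precision.* Allocation is in blocks ("four people will always be randomized (two for intervention and two for the control group"), which makes 10 rounds and 9 extra parameters as fixed terms. In the simulated median regression with baseline AES included, adding them gave SEs of 4.1-4.3, 3.7-3.9 and 3.2 for r = 0.3, 0.5 and 0.7 with an intraclass correlation of 0 to 0.05: no gain and usually a small loss. A random intercept is not part of ordinary median regression.
- *That baseline AES is the largest gain available.* This depends on r, and at 0.3 the gain is negligible.
- *That the gain makes up for drop-out.* With 14 per arm, power at d = 0.91 goes from 64% to 76% (r = 0.5) or 90% (r = 0.7), but that compares a covariance analysis with an unadjusted t test. The article says "For simplicity, sample size considerations are based on a Student’s" t test, whereas the planned analysis is a median regression with two covariates, for which the increment is smaller.

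**Conclusion.** The point holds as one of efficiency and specification. Baseline AES is not named, the form of the AES outcome is not fixed, and the two covariates are not restricted to baseline. Against the planned two-covariate median regression, adding baseline AES lowers the SE by nothing at r = 0.3, about 10% at r = 0.5 and about a quarter at r = 0.7. These figures assume SD 11, normal errors, 20 evaluable per arm and correlations of 0.3 for the planned covariates; none of the correlations is in the article. They also assume that AES is among the questionnaires given at baseline.

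A reader might infer that the planned comparison is biased or its test invalid. It is not: randomisation protects the comparison without baseline AES, and the standard error reflects chance imbalance. Distortion would arise only if a post-intervention covariate were used, which the text permits but does not plan.

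**What to change.** State the primary model as a median regression of post-intervention AES on arm, baseline AES, baseline dementia severity and baseline depression. Write that no covariate measured after randomisation enters any between-group model. In the between-group secondary models for people with dementia, add the outcome's own baseline value wherever Multimedia Appendix 1 shows that one is collected. If the blocked allocation is to be reflected, do so in a sensitivity analysis with round, without claiming precision for it.

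The cost is one degree of freedom per model and a change of wording, with no additional data if AES is measured at baseline as Table 1 suggests. Because the trial is under way, the change should be dated and recorded before outcome data are analysed by arm.

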#### Primary Aims

The primary aims of this study include exploring the effect of Coach Robot Pepper on motivation (in the sense of increased, decreased, or stable apathy) of people with dementia versus the tablet PC–based training, and exploring the effect of Coach Robot Pepper on the care burden of relatives compared with the tablet PC–based training.

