#### Secondary Aims

There are several secondaru aims of this study, one of which is exploring the effect of Coach Robot Pepper on acceptance, usability, quality of life, cognition, mobility, depression, behavioral problems, and care dependency of people with dementia versus the tablet PC–based training. We would also like to explore the effect of Coach Robot Pepper on depression, quality of life, affect and acceptance, and usability of relatives versus the tablet PC–based training. There will also be a supplementary investigation of the acceptance and usability of robot Pepper and the tablet PC–based training in dementia trainers and caregivers, a supplementary observation of people with dementia to get an insight into how to handle a robot and the tablet PC–based training in home care (including usability), and supplementary interviews (focus groups or individual interviews) to obtain a deeper understanding of the experience (including usability) of all participants using Coach Robot Pepper in home care.

The description of the study protocol follows the Standard Protocol Items: Recommendations for Interventional Trials guideline [29].

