##### Care Burden

The Zarit Burden Interview will be used to measure the subjective care burden of the relatives. The instrument has 22 items (5-point Likert scale), and a total of 0-88 points can be obtained. Higher scores indicate greater caregiver distress [36-38].

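### Relatives' care burden is a primary outcome compared between arms, but the only analysis that covers it is a pre-post paired test with no treatment-group term

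*Protocol article*

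**What the plan says.** Under Primary Aims, the second of two aims is "exploring the effect of Coach Robot Pepper on the care burden of relatives compared with the tablet PC–based training". Under Primary Outcome Measurements, Care Burden, the article adds: "The Zarit Burden Interview will be used to measure the subjective care burden of the relatives". The scale runs from 0 to 88. The design is randomised, parallel and two-arm, with 40 relatives planned, 20 per group.

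The Quantitative Analysis section then gives three pieces:

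- For the primary question: "To answer the primary question as to whether the motivation differs between the two intervention groups, a median regression is planned".
- For secondary outcomes: "For differences between the intervention groups for the secondary outcomes, the ordinal scale data will be analyzed with median regression". Metric data get a covariance analysis. The adjustment is for degree of dementia and depression.
- For relatives: "Changes in pre- and postintervention outcomes concerning relatives will be analyzed by a paired" t test or a two-tailed Wilcoxon signed-rank test, chosen by the distribution of the data.

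Relatives' secondary aims are also worded as a comparison: "explore the effect of Coach Robot Pepper on depression, quality of life, affect and acceptance, and usability of relatives versus the tablet PC–based training".

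**The concern.** A paired t test or signed-rank test of pre-post change asks whether a set of people changed. It contains no contrast between randomised groups. Run within one arm, it tests change in that arm. Run on all relatives together, it tests change in relatives as a whole. Neither estimates the effect of Coach Pepper relative to the tablet training, so for this primary outcome the randomisation goes unused.

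The control group is active. It gets the same tablet training, weekly trainer visit, two observation visits and regular calls. Burden scores could therefore move in both arms because of what the arms share, because of taking part in a study, or through regression to the mean. A paired test cannot separate any of these from an effect of the robot.

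**Working it through.** **Step 1. Which sentence covers care burden?**

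| Analysis sentence | Stated scope | Covers Zarit? |
|---|---|---|
| Median regression | Primary question, motivation | No, a different outcome |
| Median regression or covariance analysis | Secondary outcomes, between groups | No, Zarit is primary |
| Paired t or signed-rank test | Relatives, pre-post change | Yes |

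Only the paired test remains.

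**Step 2. What does each test examine?** Let the mean change be m in the tablet arm and m + δ in the Pepper arm, with equal arms. The aim concerns δ.

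- Paired test in the Pepper arm: null hypothesis m + δ = 0.
- Paired test in the tablet arm: m = 0.
- Paired test pooled over arms: m + δ/2 = 0.
- Between-arm test: δ = 0.

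Only the last one addresses the aim.

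**Step 3. The article's own figure.** The Sample Size section states 80% power with 20 per group at effect size 0.91, two-sided 5%, two-group t test. The noncentrality is 0.91 × √(20/2) = 2.88, which gives 80.1%. With 10/11 = 0.909 the power is 80.0%. The figure reproduces. It was set out for motivation and does not bear on the mismatch, but it fixes the scale for Step 5.

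**Step 4. No true arm difference (δ = 0).** The article gives no expected change in burden, so m is an assumption, shown over a range in units of the SD of the change score. The results come from 20,000 simulated trials with normal change scores and a 5% two-sided level.

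20 relatives per arm:

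| Shared change m | Pooled paired test significant | Pepper arm only significant | Exactly one arm significant | Between-arm test significant |
|---|---|---|---|---|
| 0 | 5% | 5% | 10% | 5% |
| 0.25 | 34% | 15% | 30% | 5% |
| 0.5 | 87% | 25% | 50% | 5% |
| 0.75 | 99.7% | 10% | 20% | 5% |

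Exact check at m = 0.5. In one arm the noncentrality is 0.5 × √20 = 2.24, giving power 0.565. Pooled, it is 0.5 × √40 = 3.16, giving power 0.869. Pepper arm only: 0.565 × (1 − 0.565) = 0.246. The exactly-one-arm rate is twice that, 0.49, and half of it is the tablet arm alone. The Pepper-only column is therefore the one that would mislead in the robot's favour.

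The article assumes 20% to 30% drop-out. With 15 per arm (25% lost), the pooled test is significant in 5%, 26%, 75% and 98% of trials across the same range. Pepper-only is 5%, 13%, 25% and 18%. The between-arm test stays at 5%.

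**Step 5. The opposite error.** Take a true arm difference of 0.91 SD made of changes of +0.455 and −0.455, with 20 per arm. Then m + δ/2 = 0, and the pooled paired test rejects in 3% of trials, against 80% for the between-arm test.

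**The case against.** The strongest counter-argument concerns scope. A reader might infer that none of the relatives' outcomes has a between-arm analysis. The text does not support that. The sentence on secondary outcomes is not limited to people with dementia, and the list of secondary measurements mixes instruments for patients and relatives (WHOQOL-BREF, CES-D, Technology Usage Inventory, PANAS). On its plain wording it could cover relatives, with the paired test as an additional look at change. Two things point the other way: relatives get a sentence of their own, and the adjustment for degree of dementia suits patients. That makes the text unclear, not wrong, for secondary outcomes. It does not help care burden, which is primary.

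A reader might also infer that the investigators intend to present a pre-post change as a robot effect. Nothing in the article says so. The aims are exploratory, and the stated hypothesis and sample size reasoning concern motivation. This limits how much harm can be claimed, but it supplies no test for the second primary aim.

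The percentages above depend on an assumed shared change and are not properties of this trial. The algebra in Step 2 does not depend on that assumption.

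Finally, a separate analysis plan may exist. That would answer an omission. Here the article states a method, and the method does not fit the aim.

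**Conclusion.** The point holds for care burden. A primary outcome with a between-arm aim is assigned, as written, only a test that has no group term. This rests on the article's wording alone and needs no numerical assumption.

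How far the paired tests could mislead depends on how much burden changes in both arms, which is not documented. With no shared change, the pooled test keeps its 5% level. With a shared change of 0.25 to 0.75 SD of the change score, its rejection rate with no arm difference runs from 34% to 99.7%, and the Pepper-only pattern occurs in 10% to 25% of trials. These figures assume 20 per arm and normally distributed change scores.

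For relatives' secondary outcomes the conclusion is weaker: the article should say which sentence applies to them. The care-burden sentence should be corrected before the data are analysed.

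**What to change.** Replace the sentence on relatives with text to this effect: the post-intervention Zarit score is compared between arms with the between-group methods the article already names (covariance analysis if the score is treated as metric, median regression if ordinal). The model includes treatment group and the relative's own baseline score, and the adjusted difference is reported with its 95% CI.

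Add that relatives' secondary outcomes measured before and after the intervention are compared between arms in the same way. Keep pre-post changes within each arm as description only.

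The cost is one or two sentences in the analysis section or the analysis plan. Table 1 already schedules questionnaires before and after each round, so no new data are needed. The article reports the study as still in its intervention stage, so at that point the change could be made before analysis.
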